
### Intervention and Comparator

Participants in the exercise group will receive 26 weeks of a home-based, virtually supervised combined endurance and resistance training program. Participants will be provided with required exercise equipment to allow them to exercise at home, including a treadmill, free weights, an exercise bench, and a mat. Exercise equipment will be delivered directly to a participant’s residence for in-home use.

Virtually supervised sessions will be delivered using the Zoom platform (Zoom Video Communications, Inc) by the Movement Revolution, Inc team of Neuro Exercise Specialists (Chicago, IL). All sessions during weeks 1‐2 will be supervised, and they will consist of familiarization sessions led by a Neuro Exercise Specialist who will educate participants on correct and safe use of exercise equipment, including a treadmill and weights. The Neuro Exercise Specialist will review how to get on and off the treadmill safely, how to use handrails on treadmills to assist with balance if needed, and correct form for lifting weights. Participants will also be instructed not to multitask or have distractions around that could increase the risk of falls and never to exercise when feeling lightheaded or dizzy or when Parkinson symptoms are worse than usual. By the end of week 2, trainers will ensure that participants can exercise safely and independently before reducing the number of supervised sessions. If participants or the Neuro Exercise Specialist still have concerns for safety after the initial 2 weeks of training sessions, participants will continue supervised virtual sessions or come to the research center for in-person exercise supervision.

Weeks 3‐6 will include 10 supervised sessions and a ramp-up phase that will include gradual increases in HR for endurance exercise and weights and repetitions for resistance exercises. If a participant is unable to do a particular exercise, the trainer will make modifications as appropriate. By the end of week 6, participants will be exercising 5 days per week (3 days of endurance training and 2 days of resistance training) at their prescribed endurance and resistance intensities. Weeks 7‐26 will be the full intervention and will include 1 supervised session per week.

Endurance training will be performed 3 times per week on a treadmill to target 80%‐85% of their HRmax for a duration of 40 minutes (30 minutes on the treadmill at target HR with 5 minutes each for warm-up and cool-down).

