Participants will be provided with an HR monitor (Polar H10), paired with the Polar Beat app (Polar) on their smartphone, to allow tracking of HR and activity by the participant and investigative team. The study team will review and download HR data for each exercise session and enter it into a secure electronic database. Participants will ramp up their exercise intensity to achieve their target HR zone over the first 6 weeks of the study. Endurance exercise will begin at 60% HRmax and progressively increase to 80%‐85% HRmax by week 6. Participants will be instructed on monitoring HR and adjusting the exercise intensity to remain in the target HR zone by changing treadmill speed and/or incline. Weekly phone calls will coach participants on adjustments to continue exercising at 80%‐85% HRmax.

Resistance training will be performed 2 times a week, with sessions separated by 48 hours. Resistance exercise sessions should be about 1 hour in length but will vary by participant. One repetition maximum (RM) will be calculated for each participant using the following formula: 1RM=weight × (1+0.0333 × repetitions). Participants will start with a training load that is 60% of 1RM. The full volume exercise prescription will consist of 5 minutes of dynamic warm-up followed by 5 exercises using free weights to improve strength and muscle mass (performed for 3 sets of 12‐20 repetitions) and one isometric strength exercise for core stabilization (performed for 1 minute). Exercises will be divided into 2 circuits: one will focus on arms, back, and core, while the other will focus on legs and core. After the first 13 weeks, resistance exercises will be changed in each circuit to continue to challenge participants, but they will still target the same muscle groups (Table S1 in Multimedia Appendix 1).

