#### Primary Outcomes

The primary outcomes for the study are feasibility, adherence, and safety of the combined exercise intervention. Adherence and feasibility will only be evaluated in the exercise group. Feasibility will be measured using the average percentage of HRmax for endurance exercise sessions and the average repetition maximum for resistance exercise sessions. Adherence will be measured using the average number of days exercised per week, the duration of exercise for resistance exercise, and the duration of exercise at target HR intensity for endurance exercise. Participants will keep track of exercise sessions using exercise diaries, which investigators will use to assess adherence. Data from Polar HR monitors will be used to assess feasibility. Safety will be measured by the incidence of adverse events (AEs) and serious AEs in the exercise and control groups.

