#### Statistical Methods for Primary and Secondary Outcomes

The primary outcomes are feasibility, adherence, and safety of the combined exercise program. To assess feasibility, we will estimate the overall average %HRmax for endurance training and average repetition maximum for resistance training and their corresponding 95% CIs for the exercise group at 26 weeks. We will then compare the average to the intended target intensity (82.5% for endurance exercise and 10-RM for resistance training) using a 1-sample *t* test (*α*=.05). We will use repeated measures ANOVA of weekly %HRmax and linear mixed models to assess any trends over time from weeks 7 to 26, including a random effect for time within participant as sample size permits. To measure adherence in the exercise group, the average number of days per week exercised and the duration of time (minutes) exercised at the specified intensity will be calculated. Achievement of the adherence (hypothesized to be at least 3 d/wk) will be tested using 1-sided, 1-sample Student independent group *t* tests. To assess safety, the incidence of individual AEs (including serious AEs) and exact CIs will be calculated. We will use Fisher exact or Poisson exact tests to compare exercise and control groups for AEs that are definitely, probably, or possibly related to the exercise intervention as categorical variables.

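### The resistance-training feasibility test uses a null value (10-RM) that contradicts the prescribed 12 to 20 repetitions, so a fully compliant group would be declared off target

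*Protocol article*

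**What the plan says.** Feasibility is one of three primary outcomes and is evaluated in the exercise group only. Its resistance component is "the average repetition maximum for resistance exercise sessions" (Protocol article, Primary Outcomes), and Table 1 sets the assessment window at weeks 7 to 26.

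The section Statistical Methods for Primary and Secondary Outcomes estimates the average with a 95% CI and continues: "We will then compare the average to the intended target intensity (82.5% for endurance exercise and 10-RM for resistance training". The comparison is a one-sample t test at the 5% level. The section does not say whether this test is one- or two-sided.

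The section Intervention and Comparator describes what participants are asked to do:

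- The start: "Participants will start with a training load that is 60% of 1RM".
- Weeks 3 to 6 are a ramp-up with "gradual increases in HR for endurance exercise and weights and repetitions for resistance exercises". Participants are to be at their prescribed intensities by the end of week 6.
- The full-volume prescription has five free-weight exercises, "performed for 3 sets of 12‐20 repetitions", plus one isometric core exercise.
- 1RM is obtained from a formula that links load and repetitions: "1RM=weight × (1+0.0333 × repetitions").

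The figure 10-RM appears only in the statistical section. Nothing in the intervention text prescribes it.

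**The concern.** The null value of a feasibility test should stand for the intensity that the intervention asks for. For endurance training it does. For resistance training it is a single value that the repetition range excludes.

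At stake is half of the feasibility outcome. Tested as written, a significant departure from 10-RM could mean that participants followed the prescription, and a non-significant result could mean that they did not. The result could not be interpreted as evidence for or against feasibility.

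**Working it through.** **Inputs (Protocol article)**

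- Null value: 10-RM for resistance, 82.5% HRmax for endurance (Statistical Methods for Primary and Secondary Outcomes).
- Full-volume repetitions: 12 to 20 per set. Formula: 1RM = w × (1 + 0.0333 × r), with load w and repetitions r (Intervention and Comparator).
- Endurance zone: 80% to 85% HRmax (Explanation for the Choice of Comparator).
- Exercise group: 16 recruited (Sample Size). With 12% attrition, 16 × 0.88 = 14.1, so n = 14 and n = 16 are both used.

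**Step 1. Endurance target.** (80 + 85)/2 = 82.5%. It reproduces exactly as the midpoint of the prescribed zone.

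**Step 2. Resistance target on the load scale.** Rearranging the formula, the heaviest load that can be lifted r times is w/1RM = 1/(1 + 0.0333 × r).

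| r | 1 + 0.0333 × r | Load as % of 1RM |
|---|---|---|
| 10 | 1.3330 | 75.0 |
| 12 | 1.3996 | 71.5 |
| 16 | 1.5328 | 65.2 |
| 20 | 1.6660 | 60.0 |

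The article does not say that sets go to failure, so the percentages for 12 to 20 repetitions are upper bounds. The 10-RM target lies above all of them, by at least 75.02 − 71.45 = 3.6 percentage points (12 repetitions) and up to 75.02 − 60.02 = 15.0 (20 repetitions). No part of the prescribed range reproduces 10-RM.

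**Step 3. Consequence for the test, on the repetition scale.** Suppose each participant's weeks 7 to 26 average lies anywhere from 12 to 20. The mean is then at least 12. To find the result most favourable to not rejecting 10, take the spread as large as the range allows: k participants at 20 and n − k at 12.

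With m the mean excess over 10 and σ² the variance with divisor n, t = √(n − 1) × m/σ, where m = 2 + 8k/n and σ² = 64 × k(n − k)/n².

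- n = 14, k = 2 gives the smallest value: m = 3.143, σ = 2.799, t = 3.606 × 3.143/2.799 = 4.05. Two-sided 5% critical value 2.16.
- n = 16, k = 3 gives the smallest value: m = 3.5, σ = 3.122, t = 3.873 × 3.5/3.122 = 4.34. Critical value 2.13.

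A general bound covers every other pattern. For values with excess between 2 and 10, σ² ≤ (10 − m)(m − 2), and m²/[(10 − m)(m − 2)] is smallest at m = 10/3, where it equals 11.11/8.89 = 1.25. Hence t ≥ √(n − 1) × √1.25, which is 4.03 for n = 14 and 4.33 for n = 16. No assumed SD is needed. The departure is always towards more repetitions, that is, lighter loads.

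**The case against.** **The metric is not defined, so the conflict might be only apparent.** If 10-RM meant a load fixed from the baseline 1RM, a participant who became stronger could lift it within the prescribed range. The gain needed is 1.3996/1.3330 − 1 = 5.0% for 12 repetitions and 1.6660/1.3330 − 1 = 25.0% for 20. This is arithmetically possible. But the article does not say it, and calling 10-RM the intended intensity does not suggest it. What stands is that the reference strength has to be stated.

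**The appendices may give a load progression.** The exercise list and sample schedule in Multimedia Appendices 1 and 2 are not shown. A progression there could explain the loads, but it would not remove the 12 to 20 repetitions in the article.

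**The consequence is limited.** The mean is reported with a 95% CI, which can be read against any target. The article sets no go/no-go rule and no pass or fail for individuals, and the endurance component is unaffected. All of this is true. It limits the damage to one null value, but that value belongs to a primary outcome.

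**Two stronger readings go too far.** A reader might infer that the 60% starting load proves the conflict, since (1/0.6 − 1)/0.0333 = 20.0, a 20-RM. It does not: this is a starting load, weights rise in the ramp-up, and feasibility is assessed only from week 7.

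A reader might also infer that the average is not one quantity, because "After the first 13 weeks, resistance exercises will be changed in each circuit to continue to challenge participants". The documents do not support that either. An r-RM is already relative to capacity on the lift concerned, and how the average is formed may be left to the full protocol or analysis plan.

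**Conclusion.** The point holds as a contradiction between two stated values. The feasibility null value of 10-RM (75.0% of 1RM) lies outside a prescription of 12 to 20 repetitions (at most 71.5% to 60.0%). The repetition range alone carries this.

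The statement that a fully compliant group would be declared off target rests on three assumptions: the measure is read in repetitions relative to current strength, every participant's average lies in 12 to 20, and the test is two-sided. Under these, t is at least about 4 for 14 to 16 participants, roughly twice the critical value. If sets stop short of failure, the repetition maximum of the loads used is higher than the count performed and lies further from 10, although the upper limit of 20 behind the bound on t then no longer applies.

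This is a statement about the group test, not about any participant failing a target. It should be corrected before the analysis.

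**What to change.** 1. Reconcile Intervention and Comparator with Statistical Methods for Primary and Secondary Outcomes, so that the prescription and the feasibility null value state the same resistance intensity. Which of the two stands is for the investigators to settle.
2. State whether repetition maximum is relative to current or to baseline 1RM.
3. Compare the mean and its 95% CI with the reconciled target.

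The article plans analysis from June 2026, so this can be settled before results are seen. The cost is wording, provided that session weights and repetitions are recorded. The article mentions an exercise diary for each session but does not list its fields, and it does not say whether 1RM is re-estimated during the trial. If current 1RM is chosen as the reference, both need checking first.

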### Explanation for the Choice of Comparator

The exercise intervention for this study is a combined endurance and resistance exercise intervention. This intervention was chosen as it has high clinical relevance–an ideal exercise prescription for PD includes both exercises to target the cardiopulmonary and musculoskeletal systems [28]. For this combined intervention, the frequency of endurance exercise is 3 times per week, and resistance exercise is 2 times per week. The endurance exercise protocol was modeled after the Study in Parkinson’s Disease of Exercise Phase III clinical trial [30]. Endurance exercise will be performed at a high intensity with a target HR zone of 80%‐85% of maximal heart rate (HRmax). Treadmill exercise was chosen as it allows participants to follow a regular rhythmic stimulus and allows participants to keep a consistent speed and grade, which should help maintain HR in the target zone. The 80%‐85% HRmax zone is calculated using a measured HRmax from a baseline cardiopulmonary exercise test. Using a measured HRmax instead of estimating with equations is particularly important in PD, as there may be increased prevalence of autonomic dysfunction affecting HRmax in PD [31]. The resistance training protocol chosen for this study is modeled after a resistance training program in PD participants with similar disease stage and study duration as our proposed study [32].

The control group was chosen to test the hypothesis that the combined endurance and resistance exercise intervention benefits cognition and motor signs of PD more than best medical management, which usually involves prescribing anti-Parkinson medication but no exercise. Few studies have looked at a combined endurance and resistance exercise intervention in PD. This study will demonstrate how a combined intervention may benefit cognitive and motor signs of the disease and influence circulating biomarkers compared to usual care.

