### Outcomes

#### Overview

The outcomes for EXCEL-PD are listed below as well as in Table 1, which includes the domain, measure, metric, method of aggregation, and time point for each outcome.

**Table 1. T1:** EXCEL-PD^a^ trial outcomes.

Outcome measure	Domain	Specific measurement variable	Metric	Method of aggregation	Time points
Primary outcomes					
Feasibility	Feasibility	Average % HRmax^b^ and RM^c^	Value at time point assessed	Mean, SD, median, range	Weeks 7‐26
Adherence	Adherence	Number of days exercised per week and duration at target intensity per session	Value at time point assessed	Mean, SD, median, range	Weeks 7‐26
Safety	Safety	Incidence of adverse events and serious adverse events	Number of events	Number and rate of events	Continuous
Secondary outcomes					
Global cognitive function	Cognitive function	Montreal Cognitive Assessment Scale	Score at time point assessed	Mean, SD, median, range	Screening and 26 weeks
MDS-UPDRS^d^ motor score (part III)	Motor sign assessment of Parkinson disease	MDS-UPDRS motor score (part III)	Score at time point assessed	Mean, SD, median, range	Baseline and 26 weeks
Klotho	Neuroendocrine	Klotho protein (nm/L)	Value at time point assessed	Mean, SD, median, range	Baseline and 26 weeks
Cortisol	Neuroendocrine	Cortisol hormone (pg/mL)	Value at time point assessed	Mean, SD, median, range	Baseline and 26 weeks
Brain-derived neurotrophic factor	Neurotrophic	BDNF^e^ protein (pg/mL)	Value at time point assessed	Mean, SD, median, range	Baseline and 26 weeks
C-reactive protein	Inflammation	CRP^f^ protein (mg/L)	Value at time point assessed	Mean, SD, median, range	Baseline and 26 weeks
Exploratory outcomes					
Domain-specific cognitive function	Cognitive function	Trail Making Test, Alternating Verbal Fluency, and NIH^g^ Toolbox	Score at time point assessed	Mean, SD, median, range	Baseline and 26 weeks
Six-minute walk	Functional capacity	Distance walked in 6 minutes in meters	Value at time point assessed	Mean, SD, median, range	Baseline and 26 weeks
VO2peak^h^	Cardiorespiratory fitness	Peak volume of oxygen consumed	Value at time point assessed	Mean, SD, median, range	Baseline and 26 weeks
Hand grip and knee extensor strength	Strength	Maximum strength (kg)	Value at time point assessed	Mean, SD, median, range	Baseline and 26 weeks

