### How Missing Data Will Be Handled in the Analysis

We will handle missing data points resulting from dropouts or noncompliance using multiple imputation methods. To fully appreciate the potential influence of missing responses, sensitivity analyses will be done to examine whether the imputation method affects outcomes and whether missing data are missing-at-random.

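### The primary adherence test compares pooled exercise days with 3 d/wk although 3 endurance plus 2 resistance days are prescribed, so the group mean can pass with little resistance training

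*Protocol article*

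**What the plan says.** The protocol article states the prescription twice. *Explanation for the Choice of Comparator* says "the frequency of endurance exercise is 3 times per week, and resistance exercise is 2 times per week". *Intervention and Comparator* dates the full schedule from the end of week 6 and gives the same split: "participants will be exercising 5 days per week (3 days of endurance training and 2 days of resistance training". Table 1 assesses adherence over weeks 7 to 26, when the full prescription applies.

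Frequency is defined as a single count, not split by modality:

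- Table 1: "Number of days exercised per week and duration at target intensity per session".
- *Primary Outcomes*: "Adherence will be measured using the average number of days exercised per week, the duration of exercise for resistance exercise", followed by endurance time at target heart rate.
- *Statistical Methods for Primary and Secondary Outcomes*: "the average number of days per week exercised and the duration of time (minutes) exercised at the specified intensity will be calculated".

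The last of these sections then sets the only adherence criterion, using a *t* test: "Achievement of the adherence (hypothesized to be at least 3 d/wk) will be tested using 1-sided, 1-sample Student independent group". It gives no reason for the value 3. No criterion is set for resistance days or for either duration.

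Two other statements bear on how the count is formed. On sources, *Primary Outcomes* assigns the heart-rate data to feasibility: "Participants will keep track of exercise sessions using exercise diaries, which investigators will use to assess adherence. Data from Polar HR monitors will be used". On missing data, the plan says "We will handle missing data points resulting from dropouts or noncompliance using multiple imputation methods", with no separate statement for adherence.

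**The concern.** Adherence is a primary outcome, and the combination of endurance with resistance training is what the article presents as new. The Discussion says the study will show whether the program can be carried out at home with high adherence. A pooled count tested against a value that endurance sessions alone can supply does not answer that question for the resistance part. The trial could report that adherence was achieved when resistance sessions were largely not done. If the 3 was meant for endurance days only, the test is set at the prescription itself and resistance frequency goes untested. The article fixes the variable, the threshold and the test, so this is not a detail left to an analysis plan.

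**Working it through.** **Inputs**

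- Prescription: 3 endurance + 2 resistance = 5 d/wk (*Intervention and Comparator*).
- Threshold: 3 d/wk, 1-sided, one sample (*Statistical Methods*).
- n = 16 in the exercise group (*Sample Size*).
- Alpha = 0.05: stated for the feasibility *t* test, assumed here for adherence.
- SD of days per week: not given; 0.5, 1.0 and 1.5 assumed.

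The article gives no derivation of the threshold, so there is no figure of its own to reproduce. The sample size rests on klotho and MoCA.

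**Step 1. Threshold as a share of the prescription.** 3/5 = 60%. A participant with 3 endurance and 0 resistance days averages 3.0.

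**Step 2. Smallest passing group mean on the pooled reading.** The formula is 3 + t(0.95; 15) × SD/√16, with t = 1.753. The last column is (mean − 3)/2, the resistance share if every endurance day is done.

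| Assumed SD | Smallest passing mean | Share of 5 d/wk | Share of resistance days |
|---|---|---|---|
| 0.5 | 3.22 | 64% | 11% |
| 1.0 | 3.44 | 69% | 22% |
| 1.5 | 3.66 | 73% | 33% |

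**Step 3. An example that needs no assumed SD.** Thirteen participants do 3 + 0 and three do 3 + 2.

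- Mean = (13×3 + 3×5)/16 = 3.375.
- Variance = (3/16)(13/16)(2²)(16/15) = 0.65, so SD = 0.806 and SE = 0.202.
- t = 0.375/0.202 = 1.86 on 15 df; 1-sided p = 0.041. The group passes.
- Resistance attendance = (3×2)/16 = 0.375 d/wk, which is 0.375/2 = 19% of the prescription.

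**Step 4. Probability of passing at a true mean of 3.6 d/wk** (all endurance and 30% of resistance, 3 + 0.3×2). By noncentral t it is 0.998, 0.74 and 0.45 for SD 0.5, 1.0 and 1.5. It depends strongly on the SD.

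**Step 5. The endurance-only reading.** Full attendance is exactly 3, so a mean above 3 requires more than the prescription. The smallest passing means in Step 2 become 3.22/3 = 107%, 3.44/3 = 115% and 3.66/3 = 122% of the prescribed endurance days. Resistance frequency has no criterion.

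**Step 6. The same 60% applied by modality.** 0.6×3 = 1.8 endurance d/wk and 0.6×2 = 1.2 resistance d/wk; together 3.0, the pooled threshold. The Step 3 group, at 0.375 resistance d/wk, falls well short of 1.2.

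**The case against.** The best defence is that 3 is only described as hypothesized. In a pilot, any floor below full attendance is a judgement, and the Discussion describes the endurance model as 3 to 4 days a week. Table 1 also promises mean, SD, median and range, and resistance duration is an adherence measure. A mean near 3.4 against 5 prescribed would therefore be visible to readers. This stands as far as it goes: 60% is not shown to be wrong as a floor. But the days are not split by modality, and the only formal criterion cannot separate the two components.

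A second objection concerns timing. Recruitment has closed, data collection ends in May 2026, and the unblinded team reviews adherence weekly. A new success rule chosen now would be set with adherence largely known. This limits the fix but does not remove the problem.

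Three stronger readings are tempting, and the document does not support them.

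- *Any participant who skips resistance training meets the criterion, so the group passes.* The test is on a group mean. If everyone averaged exactly 3.0, it would not pass.
- *Diaries push adherence upward.* Bias is not shown. Diaries cover both modalities, and heart-rate files, duration and days are reviewed weekly with the participant.
- *Imputation would turn failure into success.* The missing-data section is a general rule and does not say that unexercised days are imputed; it also plans sensitivity analyses. Suppose 2 of 16 stop after week 10 and the others average 4.5 d/wk. The stoppers then average 4.5×4/20 = 0.9. With days after stopping scored zero, the mean is (14×4.5 + 2×0.9)/16 = 4.05, with SD 1.23, t = 3.42 and p = 0.002: a pass without any imputation. With 4 stopping, the mean is 3.60 and p = 0.078. But 4/16 = 25% is about twice the planned 12% attrition, and the only two withdrawals reported are controls.

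**Conclusion.** The concern holds for the threshold and the pooled count. On the literal reading, the primary adherence test can succeed with roughly 11% to 33% of resistance days done, given full endurance attendance and an assumed SD of 0.5 to 1.5. The 13-and-3 example passes with no assumption about SD, only the assumed alpha of 0.05. On the endurance-only reading, success needs more than the prescription and resistance frequency is untested. Neither reading lets the test speak to adherence to the combined program. Calling the test both one-sample and independent-group is a separate contradiction in wording. The treatment of unexercised days and the source for minutes at target heart rate need stating, but no bias from either is established.

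**What to change.** Reconcile the statistical section with the prescription as follows.

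- Analyse endurance days per week and resistance days per week separately over weeks 7 to 26, each as a share of its prescribed 3 or 2. Compare each 1-sided 95% lower confidence limit with 60%, the share the plan already implies. Using that share avoids choosing a new threshold late.
- Base any conclusion about adherence to the combined program on both components.
- Keep the pooled 3 d/wk test as the plan specifies it, report it alongside, and date the change before analysis starts in June 2026.
- State that days not exercised, including those after a participant stops exercising, count as zero and are not missing values under the imputation rule.
- Name the recorded heart-rate files as the source for minutes at target heart rate.
- Call the test a 1-sample *t* test.

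No new data are needed: diaries and heart-rate files already record the sessions. The costs are an amendment with ethics approval, a funder report and a registry update, as *Protocol Amendments* requires, and an adherence figure that may be less favourable.

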### Sample Size

We based the sample size calculations on the secondary outcomes of efficacy. Since adherence and feasibility can only be evaluated in the exercise group and are not collected in the control group, it is not possible to calculate power comparing these outcomes between groups. The power and sample size analysis is based on the biomarker of interest, klotho, and the global cognition measure, MoCA. Based on prior studies describing changes in klotho plasma levels with exercise in healthy sedentary adults [33,34], a sample size of 14 participants per group is expected to detect an effect size of 100  pg/mL, considering a type I error of 0.05 with a statistical power of 0.85. Assuming a maximum attrition rate of 12%, we decided to recruit a total of 31 participants (16 participants in the exercise group and 15 in the control group). With respect to cognition, prior endurance exercise and resistance training studies show benefits on cognition at 6 or 12 months [17,35], but Chang et al [36] have shown that endurance exercise for 8 weeks leads to a statistically significant improvement in MoCA (1.6-point increase). Based on our sample size of 31, we will have 80% power with a 2-sided type I error of 0.05 to detect a significant improvement in MoCA.

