### Conclusions and Potential Impact of the Study

If successful, this intervention will show that a clinically relevant combined endurance and resistance exercise program is both safe and feasible and provides increased benefits to cognition and motor symptoms compared to best medical management. As there are currently no effective pharmacological treatments for cognitive impairments in PD, this study has very important clinical implications for PD treatments. We will also be able to probe the mechanisms underlying this effect using the fluid-based biomarkers collected in this trial.

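### The only between-group safety analysis is a low-powered test of no difference in about 16 vs 15 people, without an estimate of the difference, so it cannot carry the promised conclusion on safety

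*Protocol article*

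**What the plan says.** All references are to the protocol article.

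- Statistical Methods for Primary and Secondary Outcomes: "The primary outcomes are feasibility, adherence, and safety of the combined exercise program".
- Primary Outcomes: "Safety will be measured by the incidence of adverse events (AEs) and serious AEs in the exercise and control groups".
- The analysis has two parts. The first is estimation: "To assess safety, the incidence of individual AEs (including serious AEs) and exact CIs will be calculated". The second is comparison: "We will use Fisher exact or Poisson exact tests to compare exercise and control groups for AEs". The comparison covers only "AEs that are definitely, probably, or possibly related to the exercise intervention as categorical variables". No measure of the difference between groups, and no interval for it, is named.
- Sample Size: "We based the sample size calculations on the secondary outcomes of efficacy", and "we decided to recruit a total of 31 participants", 16 to exercise and 15 to control. Neither power nor precision is given for safety.
- Discussion: Principal Findings says the study will demonstrate whether the intervention is safe. Conclusions and Potential Impact of the Study says that success would show that the "combined endurance and resistance exercise program is both safe and feasible".

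**The concern.** A test of no difference can produce evidence of harm. When it is not significant, it gives no evidence that harm is absent, and in a small trial non-significance is the likely result even when the excess risk is substantial. Here that test is the only planned between-group safety analysis, the trial was sized on klotho and MoCA, and the Discussion looks forward to a conclusion on safety. If the report leans on the test, a real excess of falls or injuries among exercisers could appear as no difference from control. What is at stake is how one of the three primary conclusions is worded.

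**Working it through.** **The plan's own figure.** There is none for safety. The only related figure is the total of 31, built from 14 per group and 12% attrition: 28/0.88 = 31.8, or 28 × 1.12 = 31.4. It reproduces to within one participant and says nothing about AEs.

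**Inputs.** Group sizes 16 and 15 are from Sample Size. The two-sided alpha of 0.05 is an assumption, because no level or sidedness is stated for the safety test. All event risks are assumptions, because the article gives none.

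**1. Smallest result that is significant.** Suppose there are no events in controls. Given the total number of events, the two-sided Fisher p-value adds the probability of all events falling in the exercise group and the probability of all falling in the control group.

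- 4/16 vs 0/15: [C(16,4) + C(15,4)]/C(31,4) = (1820 + 1365)/31465 = 0.101.
- 5/16 vs 0/15: [C(16,5) + C(15,5)]/C(31,5) = (4368 + 3003)/169911 = 0.043.

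Five exercisers with an event are needed. At 4/16 (25%) vs 0/15 the Newcombe 95% CI for the risk difference runs from -0.2 to 49.5 percentage points.

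**2. Power with no related events in controls.** This is the case that best fits the planned endpoint, since waitlist controls do not receive the program during the 26 weeks. Power is P(X ≥ 5) with X ~ Binomial(16, p):

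| True risk in exercisers | Detected | Missed |
|---|---|---|
| 20% | 20% | 80% |
| 25% | 37% | 63% |
| 30% | 55% | 45% |
| 40% | 83% | 17% |

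The article reports two control withdrawals. With 13 controls, 5/16 vs 0/13 gives p=0.048 and 4/16 vs 0/13 gives p=0.107, so the table is unchanged.

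**3. Power with some events in controls.** This enumerates all tables from Binomial(16, pE) and Binomial(15, pC).

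| Control risk | Exercise risk | Detected | Missed |
|---|---|---|---|
| 5% | 25% | 20% | 80% |
| 10% | 30% | 18% | 82% |
| 10% | 40% | 38% | 62% |

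With 16 vs 13, power for 10% vs 30% is 21%.

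**4. The Poisson option.** This is the exact conditional test, with a person-time share of 16/31 for exercise. Power for a doubled event rate is 11%, 33% and 60% at 0.2, 0.5 and 1.0 control events per person. For a tripled rate at 0.2 it is 35%.

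**5. What the planned exact intervals can show.** The two-sided 95% Clopper-Pearson upper limit for 0/16 is 1 - 0.025^(1/16) = 20.6%. For 1/16 it is 30.2% and for 2/16 it is 38.3%. If the true risk were 10%, no events in 16 would still be seen with probability 0.9^16 = 18.5%.

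**The case against.** The strongest reply is that the plan already estimates, and that the rest is inferred by the reader. Several stronger readings are tempting, and the document does not support them.

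- *That no upper bound is planned.* Exact CIs for AE incidence come in the sentence just before the test, and each has an upper limit.
- *That a non-significant test will be reported as safe.* No such rule is stated. Principal Findings says whether, and the Conclusions are conditional on success.
- *That the lack of a maximum acceptable AE rate is a defect.* It may sit in the full protocol or an analysis plan that is not shown, so it is not raised here.
- *That the test misses most relevant harms, or reaches 80% power only at extreme contrasts.* The article defines no relevant harm, and 0% vs 40% has 83% power.

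It is also fair to say that the test is confined to exercise-related events, so scenarios with control risks of 10% or more describe it less well. All AEs are to be published, an independent safety monitor reviews them about every 6 months, and this is a pilot in which descriptive safety reporting is ordinary.

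All of that stands, and it narrows the point without removing it. Even with no events in controls, the case most favorable to the test, a risk of 20% to 25% is missed more often than not. Restricting the test to exercise-related events in an unexposed control group also makes the comparison less informative, so more weight falls on the exercise-arm interval. The monitor protects participants during the trial but does not supply the final inference.

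**Conclusion.** The point holds in a limited form. The article plans suitable intervals for AE incidence, but it compares the groups only by a test of no difference and names no estimate of that difference. The test could not support a conclusion of safety. With no control events assumed, it misses true exercise risks of 20%, 25% and 30% in 80%, 63% and 45% of trials; with an assumed 10% control risk, it misses 30% in 82%. The intervals are also limited: no serious AEs among 16 exercisers leaves risks up to about 21% open. The miss rates rest on assumed event risks and an assumed two-sided 0.05 level. The 21% limit rests only on n=16 and a two-sided 95% exact interval. The trial's validity is not affected; the wording of one primary conclusion is.

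**What to change.** In Statistical Methods for Primary and Secondary Outcomes:

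- Rest the safety conclusion on the exact CIs for the exercise arm, and include the proportions of participants with at least one AE and with at least one serious AE.
- Add the between-group risk difference with its 95% CI, or the rate ratio with its 95% CI where event counts are compared.
- Keep the Fisher or Poisson test as descriptive, and state that a non-significant result is not evidence of safety.

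In Principal Findings and in Conclusions and Potential Impact of the Study, limit the safety claim to the risk that the upper confidence limit excludes. With no serious AEs in 16 exercisers, for example, that is a risk above about 21%.

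This needs no new data and can be done before the analysis begins. The cost is a more modest safety claim.
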